## Abstract

**Background:**

The provision of smoking cessation support in Australian drug and alcohol treatment services is sub-optimal. This study examines the cost-effectiveness of an organisational change intervention to reduce smoking amongst clients attending drug and alcohol treatment services.

**Methods/design:**

A cluster-randomised controlled trial will be conducted with drug and alcohol treatment centres as the unit of randomisation. Biochemically verified (carbon monoxide by breath analysis) client 7-day-point prevalence of smoking cessation at 6 weeks will be the primary outcome measure. The study will be conducted in 33 drug and alcohol treatment services in four mainland states and territories of Australia: New South Wales, Australian Capital Territory, Queensland, and South Australia. Eligible services are those with ongoing client contact and that include pharmacotherapy services, withdrawal management services, residential rehabilitation, counselling services, and case management services. Eligible clients are those aged over 16 years who are attending their first of a number of expected visits, are self-reported current smokers, proficient in the English language, and do not have severe untreated mental illness as identified by the service staff. Control services will continue to provide usual care to the clients. Intervention group services will receive an organisational change intervention, including assistance in developing smoke-free policies, nomination of champions, staff training and educational client and service resources, and free nicotine replacement therapy in order to integrate smoking cessation support as part of usual client care.

**Discussion:**

If effective, the organisational change intervention has clear potential for implementation as part of the standard care in drug and alcohol treatment centres.

**Trial registration:**

Australian and New Zealand Clinical Trials Registry, ACTRN12615000204549. Registered on 3 March 2015.

**Electronic supplementary material:**

The online version of this article (doi:10.1186/s13063-016-1401-6) contains supplementary material, which is available to authorized users.

## Background

In Australia, 77–95 % of people entering drug and alcohol treatment smoke tobacco [1, 2]; this prevalence is five times that of the general adult population (12.8 % in 2013) [3]. A similar high prevalence of smoking has been reported in US [4] and UK addiction treatment facilities [5, 6]. People with substance use disorders report heavier nicotine dependence and smoke more cigarettes per day than the general population [2, 7, 8]. As a result, people seeking treatment for substance use and substance dependence experience a greater tobacco-related burden of illness [9].

Studies show that clients treated for substance use and dependence are very interested in quitting smoking and can be successful in quitting [2, 10]. Large-scale trials among alcohol-dependent patients show long-term smoking cessation of 10–15 % among those receiving counselling and pharmacotherapy [11–13]. Trials of patients on methadone maintenance programs also show cessation during treatment ranging from 9 % to 33 %, although with a high prevalence of relapse [14–16]. A review of 24 studies showed that smoking cessation intervention enhanced other drug treatment goals as well [17]. A meta-analysis comparing the safety and efficacy of quit interventions during and after addiction treatment found short-term smoking cessation was comparable for participants during treatment and those in sustained remission from substance use disorders [18]. Longer-term treatment benefits in the likelihood of abstinence from alcohol and drugs were found when smoking was addressed during, rather than after, treatment [18]. These results suggest addressing smoking with drug and alcohol clients does not impair treatment and can improve other treatment outcomes.

Tobacco treatment guidelines in Australia [19] and other countries [20, 21] recommend smokers with substance dependence be offered medication and counselling to assist quitting. Evidence-based approaches include assessing smoking status, advising smokers to quit, providing counselling/pharmacotherapy, considering treating substance abuse problems with medications that target these problems but may also help with smoking cessation (e.g., naltrexone with alcoholism), and follow up on quit attempts.

Despite the benefits, studies have found that drug and alcohol treatment centres do not routinely offer clients support with smoking cessation [22, 23]. The decision on whether they address client smoking is left to individual staff members within these centres [23–26]. Factors within treatment settings that reduce the probability of addressing client smoking include a lack of smoke-free policies, staff smoking, a smoking-permissive culture [24], and common beliefs that service users do not want to quit or that quitting will negatively impact the treatment [27].

The use of organisational change approaches to smoking cessation in drug and alcohol treatment centres is novel, and evaluations of its effectiveness in those settings remain preliminary. Organisational changes for smoking cessation involve (1) establishing systems for identifying and recording smoking status; (2) providing education, resources, and feedback to build the capacity of staff to support quit attempts; (3) dedicating staff to provide quit treatment; (4) implementing and promoting organisational policies to provide quit services; and (5) including effective smoking cessation support (both counselling and pharmacotherapy) as part of usual care [28]. Organisational change models also encourage the ‘denormalisation’ of smoking within the treatment environment. Small pilot studies suggest an organisational change approach can successfully integrate smoking cessation support into routine care provided by drug and alcohol clinics [29–32]. For example, Guydish et al. [29] report that 6 months following the introduction of the ‘Addressing Tobacco Through Organizational Change’ (ATTOC) model in three large treatment centres in the US, staff attitudes towards smoking cessation treatment, distribution of nicotine replacement therapy (NRT), and staff provision of tobacco treatments became significantly more positive. ATTOC included staff training in the core component of organisational change, policy development, leadership support, and access to NRT. The next iteration of organisational change research for smoking cessation needs to rigorously evaluate patient outcomes and costs. The protocol has been written following the SPIRIT advice (see Additional file 1).

### Study aims

The primary aim of the Tackling Nicotine Together (TNT) trial is to determine the effectiveness of an organisational change intervention in increasing smoking cessation (7-day-point prevalence of abstinence) amongst clients attending drug and alcohol treatment services. Secondary aims of the trial are to examine the cost-effectiveness of the organisational change intervention compared to usual care and to examine the effectiveness of an organisational change intervention in increasing prolonged smoking abstinence, quit attempts, and the use of cessation aids as well as reducing nicotine dependence amongst clients attending drug and alcohol treatment services. Changes in delivery of smoking cessation care to clients will also be measured.

### Hypotheses

Compared to clients in treatment centres allocated to minimal ethical care (control group), clients attending intervention services will have: (1) 9.5 % higher smoking cessation rate at the 6-week follow-up as measured by biochemically verified 7-day-point prevalence of abstinence (primary outcome measure) and (2) 8.5 % higher prolonged abstinence at the 6-month follow-up (secondary outcome measure).The organisational change intervention will be more cost-effective than usual care at 6-month follow-up.

## Methods/design

A cluster-randomised trial will be conducted with drug and alcohol treatment services as the unit of randomisation. The primary outcome measure is biochemically verified client 7-day-point prevalence of abstinence at 6 weeks. As full concealment of allocation is difficult in behavioural cluster trials, this study will use partial blinding, whereby randomisation of the clusters will be performed by a biostatistician not involved with the study and who will be blind to the identity of the treatment centres. Similarly, follow-up assessments will be conducted by interviewers blind to the experimental condition. The flow chart of the TNT trial is displayed in Fig. 1. Ethical approval for this study was obtained from the Hunter New England Human Research Ethics Committee (HREC), Australian Capital Territory Health HREC, South Australia Health HREC, and University of Newcastle HREC.

**Fig. 1 Fig1:**
[figure not shown]
Schematic of the Tackling Nicotine Together (TNT) trial study design. CATI, computer-assisted telephone interview

### Setting

The study will be conducted in 33 governmental and non-governmental drug and alcohol treatment centres in four mainland states or territories of Australia: New South Wales (NSW), Australian Capital Territory (ACT), Queensland (QLD), and South Australia (SA).

### Recruitment and randomisation of treatment centres

#### Recruitment

Eligible drug and alcohol services were those providing services involving face-to-face client sessions to a large number of clients (minimum of 50 per year) in NSW, Queensland, ACT and SA. Recruitment was conducted through key contacts (such as Directors of Health Services or peak non-governmental organisations) who assisted in recruitment. Treatment services were invited to participate by writing and followed up by telephone and in person.

#### Randomisation

Randomisation was undertaken by an independent statistician who used a combination of stratified and restricted randomisation in Stata version 13 to ensure equitable distribution across the intervention groups of stratification factors including the state/territory (NSW, Queensland, ACT, and South Australia), service type (governmental or non-governmental organisation), and smoking policy (partial or total smoking ban). Stratification based on these factors produced ten non-zero strata. Five strata included an even number of sites (24 in total), with these sites randomised within strata to either the intervention or the usual care group. The five remaining strata with an uneven number of sites were combined to form two ‘meta’ strata, based on the state (either ACT or QLD, each with *n* = 4 services) and which were also homogeneous for the type of smoking policy, and one single site strata. The PERCOM module was then used to generate all the possible combinations of treatment allocations within these two meta-strata and restricted the set of all 36 combinations of treatment allocations within strata 1 and strata 2 to be those with balance of service type between treatment arms. One of these 18 balanced allocations was then randomly selected, and finally, the remaining single site was randomly allocated using simple randomisation to either intervention or usual care. This produced a final allocation sequence that, at most, had an imbalance of one site for each stratification factor—the best that could be achieved with an uneven number of sites. All random sampling and treatment allocation was achieved by generation of random uniform values.

### Participants

Treatment service clients eligible for inclusion in the trial will be those aged over 16 years who are attending their first of a number of visits (to allow for repeated exposure to the intervention), who are self-reported current smokers, sufficiently proficient in English, and do not have severe untreated mental illness as identified by treatment staff in order to give informed consent. Informed consent will be obtained from all participants.

### Client recruitment

A staff member at each treatment centre will be trained to conduct client recruitment. Baseline client recruitment will occur over a minimum 6-month period. Eligible clients will be provided with written information about the study and, if interested in participating, asked to complete the consent form and a baseline touchscreen survey. Eligible clients will be informed that the study aims to expand the services provided by the treatment centre, it involves completing a survey about their smoking, and their carer or case-worker may discuss their smoking with them.

### Data collection

Participants will be asked to complete a baseline survey via a touchscreen tablet at the time of recruitment and an additional two surveys over the telephone after 6 weeks and 6 months. At the 6-week and 6-month follow-up assessments, allowing for a 2-week grace period post-baseline, participants who report 7-day-point prevalence of abstinence will also be asked to return to the service to provide a breath sample to measure carbon monoxide (CO).

### Retention strategies

To maximise retention of the participating clients at the 6-week and 6-month follow-up, this study will employ a number of evidence-based strategies [33, 34]. Follow-up dates and times will be set during recruitment, and participants will be provided with a TNT ‘business card’ featuring all study contact details and the 6-week and 6-month follow-up times. Detailed contact information will be obtained from clients agreeing to participate, including their current home address, phone numbers, and email addresses. These contact details will also be collected for a nominated family member or friend. Ongoing contact with the participant via regular text messages, letters, or emails will be used to remind participants to keep their contact details up-to-date with the research team and to remind them when their follow-up survey is coming up. Finally, clients will be offered monetary reimbursement (AUD$50 grocery voucher) when all assessments are completed at the 6-month follow-up for costs incurred (including travel costs and child care).

### Intervention and comparator

#### Control group

Treatment services in the control group will provide usual care.

#### Intervention group

Intervention services will participate in an ‘organisational change’ intervention which aims to establish or improve routine screening, assessment, and delivery of smoking cessation care and treatment to clients. Organisational changes integrate identifying smokers and offering cessation treatment into routine care. The main goal of the intervention is to increase the level of evidence-based brief smoking cessation advice, education, and nicotine replacement therapy offered to clients as part of their usual treatment.

The conceptual framework for the intervention is based on organisational change literature that is tailored to smoking cessation—Fiore et al.’s System Changes approach [20, 28] and Ziedonis’ ATTOC model [32]. The organisational change strategies that will be used to help build the treatment services capacity to deliver the smoking cessation support to clients are outlined below.***Engaging organisational support***. High-level support for change within the organisation is crucial for implementing change across an entire site [35]. Advocacy, staff meetings, and communications (e.g. newsletters, noticeboards, and email) will be used to sequentially engage all levels of staff and address staff and systems barriers.***Identifying and supporting a smoking cessation****‘****champion****’*. Having a key staff member who takes the lead role in ensuring smoking cessation treatment is provided to clients can improve treatment delivery and compliance [28, 32]. During training, one staff member in each treatment centre will be nominated by the group to take a lead role. That staff member will be assisted by other support staff to deliver brief advice to clients who smoke, oversee client survey recruitment, and follow up client progress.***Promoting centre policies that support and provide tobacco dependence services***. Ensuring treatment centres are smoke-free environments will address the barrier of smoking-permissive social norms [36]. On a site-specific basis, project staff will assist with implementing smoke-free policies, smoke-free signage, support for staff to quit, and changes to processes to create a cessation-supportive environment. Services that have policies in place will be assisted in developing programs to maximise enforcement. Total smoke-free policies will be the goal.***Implementing a system of identifying smokers***. The goal of this strategy is to ensure that all patients are asked about tobacco use as part of every clinical encounter. Each TNT site will be asked to develop a way for assessing and recording client smoking status using their electronic or paper-based record system. Such prompts have been shown to increase the rate that clinicians intervene with smokers [37].***Providing education and resources****(****including staff training****)*. Training is necessary to ensure that staff has the skills and information to assist their clients in making a quit attempt [28, 32]. Staff will receive training on smoking cessation techniques, focusing on the 5As (ask, assess, advise, assist, and arrange follow-up) and appropriate NRT provision in the form of a 1-day face-to-face workshop with a credited smoking cessation trainer. It is designed to encourage and support smoking cessation practices as part of routine care. The Stages of Change [10] theoretical model is used to assess a smoker’s motivation to quit and tailor support.***Providing case****-****worker and client feedback***. Computerised feedback has been found to improve the delivery of preventive services in general practice [38]. For the service, newsletters and brief update reports will be used to motivate staff and keep the service engaged with the intervention. In addition, CO monitors will be used to provide motivational feedback to clients regarding their progress during quit attempts.***Providing evidence****-****based tobacco dependence treatments****(****including NRT****)*. Tobacco dependence treatment is both clinically effective and cost-effective [36]. Providing tobacco dependence treatment within the treatment centre setting reduces the cost barriers to cessation [39]. Existing resources such as QUITline® referrals will be used where appropriate. Treatment centres will be supplied with NRT free of cost during client treatment. This intervention will provide a flexible range of NRT options and extends the limited NRT subsidies currently available through the Australian Pharmaceutical Benefits Scheme for prescription nicotine patches only.***Planning for maintenance and follow****-****up***. Hospital-based research has found that a smoking treatment summary in the discharge plan aids cessation maintenance [40]. The goal of this strategy is to ensure that clients have a plan in place to maintain cessation or to follow-up on quit interest and intentions on discharge from the service. This may include sending smoking treatment summaries to the client’s primary healthcare provider or linking the client with telephone follow-up services such as Quitline.

Each intervention site will communicate regularly with project staff to ensure that these intervention components are implemented over a 12-week period (minimum). A printed intervention manual (full version – Additional file 2; brief version – Additional file 3) will be provided to each intervention site.

### Measurements

#### Primary outcome measure

The primary outcome measure is client smoking cessation at 6-week follow-up using biochemically verified 7-day-point prevalence. The 7-day-point prevalence of abstinence will be assessed using standard items to determine the proportion of participants who have not smoked any tobacco in the preceding 7 days: ‘Have you smoked a cigarette, even a puff in the last 7 days?’ [41]. Self-reported point-prevalence abstinence at 6 weeks will be verified using measures of CO in expired air.

#### Secondary outcomes

Prolonged abstinence will be assessed using the Russell Standard criteria [42]. The quit date will be determined at the 6-week follow-up and confirmed at the 6-month follow-up, while taking into account a 2-week grace period. Additional secondary outcomes to be collected at client 6-week and 6-month follow-ups include self-reported 7-day-point prevalence of abstinence, nicotine dependence (two-item heaviness of smoking index) [43], number of cigarettes smoked, self-reported quit attempts, and self-reported use of cessation aids.

#### Baseline characteristics

A number of client sociodemographic, smoking, and clinical characteristics will be obtained, including age, gender, marital status, Aboriginal or Torres Strait Islander status, housing status, income and source of income, education, postcode, smoking profile, and other dependencies (alcohol and other drug use).

#### Cost-effectiveness

A cost-effectiveness analysis will be undertaken from the perspective of healthcare providers and patients and will compare the cost and effect from the organisational change intervention to usual care. Costs will be stratified according to whether they fall to the health provider or patient. Health provider costs will include the cost of materials used for education and promoting smoking cessation (but not the research and development cost for preparing the materials), clinical time, case worker time, and the cost of resources committed to cessation treatments. Patient out-of-pocket costs will also be captured. These costs will be compared against the study’s primary outcome measure: 7-day-point prevalence for smoking abstinence at 6-week follow-up. The analysis will compare relative costs and outcomes in the intervention and control centres and report the incremental cost-effectiveness ratio (ICER). A sensitivity analysis will be conducted using variables with uncertain values. The results will be considered in context of strength of evidence, capacity of the intervention to reduce inequity, feasibility, sustainability, and potential for other consequences.

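### The cost-effectiveness hypothesis is set at 6 months, but the planned ICER uses abstinence at 6 weeks, so the analysis as written does not test the hypothesis

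*Protocol article*

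**What the plan says.** The article gives two time points for one question.

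- Hypotheses: "The organisational change intervention will be more cost-effective than usual care at 6-month follow-up".
- Cost-effectiveness: costs are to be set against the primary outcome, "7-day-point prevalence for smoking abstinence at 6-week follow-up". The ICER to be reported is the one from this comparison.

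The Study aims section names cost-effectiveness as a secondary aim and gives no time point. The Cost-effectiveness section states no period over which costs are counted and names no 6-month effect. Its only provision for uncertainty is general: "A sensitivity analysis will be conducted using variables with uncertain values".

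Abstinence at 6 months will nevertheless be measured. Under Data collection, clients who report 7-day abstinence at either follow-up are asked for a CO breath sample. Under Secondary outcomes, prolonged abstinence is assessed, and self-reported 7-day abstinence is listed at both follow-ups. CO-verified 7-day abstinence at 6 months is not listed as an outcome, although the sample for it is to be collected.

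**The concern.** An ICER is tied to the time at which its effect is read and the period over which its costs are counted. An ICER with a 6-week effect gives the cost per additional short-term quitter. It cannot show whether the intervention is cost-effective at 6 months, because the 6-month difference between arms does not enter it.

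Cost-effectiveness is named as the study purpose in the abstract's background, is a secondary aim, has its own hypothesis, and is a condition for longer-term use in the Discussion. If the text is followed, that hypothesis goes untested. If the conflict is left until the data are in, either time point could be chosen with the results in view.

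**Working it through.** **1. The passages side by side.**

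| Element | Hypotheses | Cost-effectiveness |
|---|---|---|
| Time of the claim or effect | 6 months | 6 weeks |
| Effect measure | not named | 7-day point prevalence |
| Cost horizon | not given | not given |

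No other section bridges the two. The conflict follows from the text and needs no arithmetic.

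**2. What the mismatch could do to the ICER.** The article states no ICER, so there is no figure to reproduce. Let C be the incremental cost per client, taken as equal in both calculations, and D the difference in abstinence between arms. Then ICER = C / D, and

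ratio of the 6-month to the 6-week ICER = D(6 weeks) / D(6 months).

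Inputs: control abstinence at 6 weeks of 5% (Sample size) and a hypothesised 6-week difference of 9.5 points (Hypotheses), which puts the intervention arm at 5 + 9.5 = 14.5%. The document does not quantify relapse. The shares of 6-week quitters still abstinent at 6 months are therefore assumptions, with no late quitting:

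D(6 months) = 14.5 × r(intervention) − 5 × r(control).

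| r intervention | r control | D at 6 months (points) | Ratio 9.5 / D |
|---|---|---|---|
| 90% | 90% | 13.05 − 4.5 = 8.55 | 1.11 |
| 70% | 70% | 10.15 − 3.5 = 6.65 | 1.43 |
| 50% | 50% | 7.25 − 2.5 = 4.75 | 2.00 |
| 50% | 90% | 7.25 − 4.5 = 2.75 | 3.45 |
| 90% | 50% | 13.05 − 2.5 = 10.55 | 0.90 |
| 100% | 30% | 14.5 − 1.5 = 13.0 | 0.73 |
| 30% | 70% | 4.35 − 3.5 = 0.85 | 11.18 |
| 30% | 90% | 4.35 − 4.5 = −0.15 | sign changes |

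A ratio above 1 means that the 6-week ICER looks more favourable than the 6-month one. Equal proportional relapse in both arms always gives a ratio above 1. Heavier relapse in the control arm can take it below 1. Late quitting could do the same: a 6-month difference of 11 points (assumed) gives 9.5 / 11 = 0.86.

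**3. The cost horizon.** The table holds C fixed. If costs were counted to 6 weeks in one ICER and to 6 months in the other, the ratio would be multiplied by C(6 months) / C(6 weeks), which the article does not allow one to evaluate. If costs to 6 months were set against a 6-week effect, later spending would be charged to an early result, which could count against the intervention.

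**4. Precision at 6 months.** From about 450 per arm at baseline, the Sample size section expects 40% loss at 6 weeks and 50% at 6 months: 450 × 0.6 = 270 and 450 × 0.5 = 225 per arm. The same section puts the detectable difference at 9 points at 6 weeks and at 10–11 points for binary outcomes at 6 months. The latter exceeds the 8.5 points hypothesised for prolonged abstinence.

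**The case against.** The best defence is that the 6-week effect is the trial's primary outcome. It is CO-verified, suffers less attrition, and is a natural denominator for an ICER. On this view the slip is in the hypothesis, and the analysis plan still to be written can settle it. Part of that stands: moving the hypothesis to 6 weeks would also remove the conflict, and a 6-month ICER would be less precise. But both time points are already in print, so a later plan can only resolve the matter by overriding one of them. This is a contradiction and not detail left out of a condensed article.

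A reader might infer more than the article supports:

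- *That the planned ICER is biased in favour of the intervention.* The direction is not established. Relapse may differ by arm, late quitting is possible, and the cost horizon is unstated. The Background does mention relapse, "although with a high prevalence of relapse", but about trials in methadone maintenance. The services here are broader.
- *That the ICER is 12% too low on the protocol's own figures.* The ratio 9.5 / 8.5 = 1.118 sets verified point prevalence at 6 weeks against prolonged abstinence at 6 months. These are different measures, so it does not show how far one effect fades.
- *That the effect is read half-way through a 12-week intervention.* The 12-week minimum is the time for a site to put the components in place. The 6 weeks run from each client's baseline, and clients are recruited over at least 6 months. The article does not align the two clocks.
- *That training, project support or NRT are left out of the costs.* The list is introduced as what costs will include, and it names "clinical time, case worker time, and the cost of resources committed to cessation treatments", which can cover NRT. It neither claims to be complete nor excludes these items.

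**Conclusion.** The point holds in a limited form. The planned ICER, with its effect at 6 weeks, does not test a hypothesis set at 6 months. That rests on the text alone.

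The size of the consequence is conditional. At equal incremental cost, and taking the protocol's 5% control abstinence and 9.5-point difference at 6 weeks, equal retention of 90%, 70% or 50% in both arms makes the 6-month ICER 1.11, 1.43 or 2.00 times the 6-week one. With unequal retention the ratio runs from 0.73 to above 11, and in the extreme the 6-month difference changes sign. If the effect fades, the 6-week ICER looks better than the 6-month one at the same cost. The document does not establish that it will.

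This should be reconciled before analysis. It concerns a secondary aim and does not affect the primary comparison, its power or the randomisation, so it ranks below the faults that must be put right for the trial to stand.

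**What to change.** In the Cost-effectiveness section:

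1. State the period over which costs are counted.
2. Add an ICER defined as incremental cost to 6 months per additional abstainer at 6 months, and name it as the analysis that tests the 6-month hypothesis. The effect can be CO-verified 7-day point prevalence or prolonged abstinence; choose one in advance. If the former is chosen, list it as a 6-month outcome.
3. Keep the 6-week ICER alongside it, labelled as cost per short-term quitter.

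The alternative is to restate the hypothesis at 6 weeks and limit the conclusion to short-term quitting. That is simpler, but says less about longer-term use.

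Cost of the main option: no new visit or test is needed for the effect, since the 6-month interview and breath sample are already planned. The 6-month ICER will be less precise, with about 225 instead of 270 clients per arm. Cost items must also be captured to 6 months, and the article does not say whether this is already planned.
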